## Abstract

**Background:**

Diabetes affects over 20 million Americans, resulting in substantial morbidity, mortality, and costs. While medications are the cornerstone of secondary prevention, many evidence-based therapies are underutilized, and patients often cite out-of-pocket costs as the reason. Value-based insurance design (VBID) is a 'clinically sensitive' refinement to benefit design which links patient cost-sharing to therapy value; the more clinically beneficial (and valuable) a therapy is for a patient, the lower that patient's cost-sharing should be. We describe the design and implementation of MHealthy: Focus on Diabetes (FOD), a prospective, controlled trial of targeted co-payment reductions for high value, underutilized therapies for individuals with diabetes.

**Methods:**

The FOD trial includes 2,507 employees and dependents with diabetes insured by one large employer. Approximately 81% are enrolled in a single independent-practice association model health maintenance organization. The control group includes 8,637 patients with diabetes covered by other employers and enrolled in the same managed care organization. Both groups received written materials about the importance of adherence to secondary prevention therapies, while only the intervention group received targeted co-payment reductions for glycemic agents, antihypertensives, lipid-lowering agents, antidepressants, and diabetic eye exams. Primary outcomes include medication uptake and adherence. Secondary outcomes include health care utilization and expenditures. An interrupted time series, control group design will allow rigorous assessment of the intervention's impact, while controlling for unrelated temporal trends. Individual patient-level baseline data are presented.

**Discussion:**

To our knowledge, this is the first prospective controlled trial of co-payment reductions targeted to high-value services for high-risk patients. It will provide important information on feasibility of implementation and effectiveness of VBID in a real-world setting. This program has the potential for broad dissemination to other employers and insurers wishing to improve the value of their health care spending.

## Background

### Medication adherence in diabetes

As health care costs continue to increase, payers are searching for innovative interventions to strike a balance between containing costs and improving health outcomes, particularly for those with chronic conditions such as diabetes mellitus. An estimated 7% of Americans, representing 20.8 million people, have diabetes [1] and the prevalence continues to rise [2]. The micro- and macro-vascular complications of diabetes result in substantial morbidity and mortality [3] and contribute significantly to health care spending in the United States [4].

Medications are the cornerstone of secondary prevention for individuals with diabetes. Randomized controlled trials and national guidelines support the use of intensive glucose, blood pressure, and lipid management to reduce rates of serious complications and death [5]. Yet, medication adherence remains suboptimal [6,7]. In turn, poor adherence is associated with disease progression and complications, avoidable hospitalizations, increased health care costs, lost productivity, premature disability, and even increased mortality [8-12]. Further, it appears that depression, which often co-exists with diabetes, is associated with worse adherence, poorer health outcomes, and higher costs in individuals with diabetes [12-15].

### Impact of co-payments on adherence

While improving medication adherence is critical to improving diabetes outcomes, systematic reviews have shown little effect of informational, behavioral, and social interventions to improve adherence [16,17]. In contrast, a recent systematic review demonstrated the substantial impact co-payments have on medication adherence [18]. Cost sharing is generally applied in a non-targeted way, without regard to the medication's therapeutic benefit. Yet, this may create financial barriers to the very medications which would most benefit patients, raising two critical questions. First, can patients determine which drugs are most valuable to their own health? Second, will they choose to prioritize their medications accordingly to maximize health outcomes? Unfortunately, the evidence suggests that cost sharing indiscriminately reduces the use of both excess and essential (clear mortality and/or quality of life benefit) medications [18-24]. In turn, growing evidence suggests that individuals who decrease medication utilization due to cost have poorer health outcomes [18,21,22,24-27] and often incur higher health care costs [18,23,27].

### Value-based insurance design (VBID)

In response to growing evidence that 'one-size fits all' co-payments harm patients, a more nuanced approach to benefit design has been proposed. In this approach, co-payments are based on the expected clinical benefit from a drug, rather than solely on its acquisition cost [28-31]. Under such value-based insurance designs (VBID) the more beneficial the medication, the lower the co-payment. VBID effectively realigns the incentives faced by patients to increase utilization of and adherence to the most beneficial and valuable medications.

Interestingly, the appeal of VBID has taken root primarily outside of medicine – in the business world. In an effort to slow health care cost growth, Fortune 500 employer (and self-insurer) Pitney Bowes lowered co-payments for asthma and diabetes medications in 2001. While no rigorous evaluation was performed, they reported a one-year one-million dollar savings to the Wall Street Journal [32]. Following Pitney Bowes' lead, several other employers (*e.g*., Marriott, Procter & Gamble, Florida Power and Light) have implemented VBID programs. Employer benefit consultants (*e.g*., Hewitt, Mercer), disease management companies (*e.g*., ActiveHealth Management), pharmacy benefit managers (*e.g*., SXC Health Solutions, Prime Therapeutics) and health plans (*e.g*., Aetna) have also launched VBID-related products. While these benefit designs hold promise for improving value of care, there have been few controlled evaluations, and none that target co-payment reductions to specific services for specific patient populations. Yet, 'targeting' is critical to improving health care value. Patient risk and, therefore, benefit from health services, is heterogeneous, with most services providing significantly higher value for patients at highest risk. By altering co-payments so that the strongest incentive to take a medication is targeted to those who will most benefit from that therapy, the more likely the system will be to maximize the health returns to spending, thereby maximizing value.

## Impetus for intervention trial

### Institutional environment

In 2004, amidst pervasive gaps in both quality and access to health care and continually increasing health care costs (particularly for employers in Michigan), the University of Michigan (UM) announced a major initiative to develop, implement, and evaluate new models of care to improve the health and well-being of the UM workforce in a cost-effective manner. As part of this initiative, the MHealthy: Focus on Diabetes (FOD) trial was designed and implemented as a targeted co-payment reduction intervention for UM employees and their dependents with diabetes. The intervention was designed as a prospective controlled study to allow for rigorous evaluation of the program's impact.

### Needs assessment

Diabetes was chosen for the focus of this intervention following a needs assessment which identified diabetes as prevalent and adherence to evidence-based pharmacotherapies as suboptimal in the UM population. While the average patient with diabetes requires multiple medications for adequate glycemic control [5], over half the UM employees and dependents with diabetes were using only one hypoglycemic agent, suggesting a potential opportunity for improvement. In turn, fewer than half were on an angiotensin converting enzyme inhibitor or angiotensin receptor blocker (ACE/ARB), and only half were on HMG-CoA reductase inhibitors (statins). The critical role of co-payments was documented in a prior investigation in M-CARE (the setting of the current study), in which Ellis and colleagues found two-year statin discontinuation rates of 50% to 100%, with the highest co-payments associated with a four-fold increase in discontinuation [19].

### Therapies selected for co-payment reductions

Interventions were selected based on evidence of health benefits, guideline indications for use [5], and documented underutilization in clinical practice. They included statins, ACE/ARBs, other antihypertensives, and all hypoglycemic agents. Co-payments were also reduced for antidepressants, as evidence suggests that diabetes self-management practices (including medication adherence) are better when comorbid depression is adequately treated [33].

## Methods

### Study overview

The aim of this study was to examine the impact of targeted co-payment reductions (targeted to high-value but underutilized services) for an employed population with diabetes. The intervention, initiated on 1 July 2006, comprised two elements: an educational letter detailing the importance of medication adherence in diabetes, and targeted co-payment reductions for several high-value therapies. The intervention group received both elements (detailed below), while a control group received the educational letter alone.

### Hypotheses

We hypothesized that the removal of financial barriers to evidence-based, high-value therapies will result in improved uptake and adherence, and a more efficient use of resources. Specific hypotheses are:

1. Compared to individuals with diabetes with usual co-pays, those receiving targeted co-payment reductions for high-value therapies will increase uptake of these therapies and improve adherence to these therapies (conditional upon their use).

2. Compared to payers for individuals with diabetes with usual co-pays, payers for those receiving value-based co-payment reductions will incur higher pharmaceutical spending, lower non-pharmaceutical cost growth, and lower overall cost growth. Importantly, we do not hypothesize an absolute financial savings over previous years. Rather, we posit that the rate of non-pharmaceutical cost growth will be slower in the intervention group than in the controls.

3. Among individuals with diabetes and depression, compared to individuals with usual co-pays, individuals receiving value-based co-payment reductions for high-value therapies will have improved uptake and adherence to antidepressants and improved uptake and adherence to other study medications (statins, ACE/ARBs, other antihypertensives and glycemic agents).

### Study setting

The University of Michigan is a large Midwestern university with an enrollment of nearly 50,000 students. The university contracts with a single pharmacy benefits manager (PBM), SXC Health Solutions, for all of its employees, dependents, and retirees. Retirees were excluded from this study, however, because Medicare Part D and the FOD intervention were implemented in close proximity, making it difficult to isolate the effects of each from the other. The approximately 70,000 active UM employees and dependents are enrolled in several different health plans. The most frequently chosen plan is M-CARE, which, in 2006, enrolled approximately 81% of active UM employees and dependents.

M-CARE is a UM-owned non-profit independent-practice association model health maintenance organization (HMO) with approximately 200,000 enrollees throughout Southeastern Michigan in 2006. While UM enrollees use the university-contracted PBM (SXC Health Solutions), all other M-CARE enrollees receive pharmacy services through CatalystRx, the M-CARE-contracted PBM at the time the FOD intervention was initiated. Both SXC and CatalystRx use the same claims processing platform, allowing for acquisition of comparable data for both the intervention and control groups in this study.

M-CARE has a diabetes disease management program designed to improve patient adherence to recommended diabetes care processes. Therefore, any measured effect of targeted co-payment reductions is actually the incremental additional effect beyond the impact of the disease management program.

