#### Data collection

Pharmacy claims were obtained for the intervention group from SXC Health Solutions, and for the control group from CatalystRx. Non-pharmacy claims were obtained from M-CARE for both groups. All data were transferred to the M-CARE claims administration office, which assigned unique study identifiers, managed the linkage of patient data across data sources and over time, and stripped the data of PHI prior to transfer to the evaluation team.

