##### Secondary outcomes

Secondary outcomes include health care utilization rates (*e.g*., counts of outpatient visits, ER visits, hospitalizations) and health care spending. Pharmaceutical and non-pharmaceutical expenditures will be examined both overall and disaggregated into the costs borne by the payer and those assumed by the patient (*i.e*., out-of-pocket costs).

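### Drug cost comes from a different pharmacy benefit manager in each group, so a one-sided price break would be read as an effect of the co-payment reduction; add a fixed-price companion analysis

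*Protocol article*

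**What the plan says.** On who pays for drugs, the article's Study setting section says of the intervention side: "The university contracts with a single pharmacy benefits manager (PBM), SXC Health Solutions, for all of its employees, dependents, and retirees". Of the control side it says: "all other M-CARE enrollees receive pharmacy services through CatalystRx, the M-CARE-contracted PBM at the time the FOD intervention was initiated". It then concludes: "Both SXC and CatalystRx use the same claims processing platform, allowing for acquisition of comparable data for both the intervention and control groups".

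The Data collection section confirms the split: "Pharmacy claims were obtained for the intervention group from SXC Health Solutions, and for the control group from CatalystRx". For everything else there is one source: "Non-pharmacy claims were obtained from M-CARE for both groups".

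Hypothesis 2 predicts that "payers for those receiving value-based co-payment reductions will incur higher pharmaceutical spending, lower non-pharmaceutical cost growth, and lower overall cost growth". The Secondary outcomes section adds: "Pharmaceutical and non-pharmaceutical expenditures will be examined both overall and disaggregated into the costs borne by the payer and those assumed by the patient". The Health care expenditures section applies the segmented multiple time-series, difference-in-difference model to log cost and plans to test a two-part model against it. The Model covariates section lists age, gender, comorbidity, member status and number of medications. None of these is a price term.

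**The concern.** Manager and study group coincide without exception for drug cost, and only for drug cost. Two separate contracts can set different unit prices and can change them on different dates. The article's reason for treating the two sources as comparable is a common processing platform. That supports comparing records, fills and days of supply, but it is silent on the amounts paid under each contract.

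Two of the three components of hypothesis 2, pharmaceutical spending and overall cost growth, use those amounts. If one manager repriced and the other did not, spending would move with no change in what patients take, and the model as described could not tell this from a response to lower co-payments. The readers whom the article addresses on cost are payers, for whom the distinction matters.

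**Working it through.** **Plan's own figure.** The article gives no figure for the cost outcomes, so there is none to reproduce. Its power figures concern uptake and possession ratios and do not bear on this point.

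**Inputs.**
- Series: 30 months before and 30 months after 1 July 2006, by quarter (Study overview; Study design). That is 10 + 10 quarters, indexed t = 0 to 19, with the intervention starting at t = 10.
- Model: log cost with group-specific segmented trends (Health care expenditures). The equation in Figure 2 is not visible, so the standard form is assumed.
- Price changes: assumed throughout, because the documents give no prices.

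**Model for the group difference.** Let D(t) be mean log drug cost in the intervention group minus that in the control group:

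D(t) = b0 + b1·t + b2·post(t) + b3·post(t)·(t − 10)

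Here post(t) = 1 for t ≥ 10; b2 is the level effect in the first intervention quarter and b3 the change in slope. The true co-payment effect is set to zero, there is no noise, and a small price change of x% is treated as x on the log scale × 100. Ordinary least squares then shows where a price change ends up.

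**What the model absorbs.**
- Constant gap: D(t) = c. Fitted b0 = c, b2 = b3 = 0.
- Steady differential drift over all 20 quarters: D(t) = d·t. Fitted b1 = d, b2 = b3 = 0.
- The same price change at both managers: D(t) = 0. All terms are 0.

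**What it does not absorb: a 5% rise in the intervention group's price relative to the control group's.**

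| Date of step | Level b2 | Slope b3 per quarter | Last quarter (b2 + 9·b3) | Mean over intervention period (b2 + 4.5·b3) |
|---|---|---|---|---|
| 1 July 2006 (t = 10) | 5.0% | 0 | 5.0% | 5.0% |
| 1 January 2007 (t = 12) | 1.82% | 0.485% | 6.18% | 4.0% |
| 1 April 2005 (t = 5, mid pre-period) | −1.67% | −0.758% | −8.48% | −5.1% |

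Check of the second row: 1.82 + 9 × 0.485 = 6.18 and 1.82 + 4.5 × 0.485 = 4.0. In the third row the step falls before the intervention. It tilts the fitted pre-trend upward, so the later series falls short of the projection and the false effect is negative.

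The fit is linear in the step. At 1 July 2006, 2% gives 2.0% and 10% gives 10.0%. A fall in the relative price reverses every sign, and a rise on the control side acts as a fall on the intervention side.

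**Overall cost.** If drugs are a share s of total cost, a false effect of 5% on drug cost becomes about s × 5% on total cost. The article gives no s, so the result lies between 0 and 5%.

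**Outcomes not directly affected.** Uptake is any fill in a year and the possession ratio counts covered days; neither uses dollars. Non-pharmaceutical cost comes from one source for both groups.

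**The case against.** The Study setting sentence claims comparable data, not comparable prices, and for the primary outcomes it is right. The article condenses a fuller plan, so silence on whether drug cost means paid amount, allowed amount or a standard price is not an error in itself. Both points stand. What remains is that the same claims also feed the spending outcomes, where a shared platform is not enough.

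The Discussion already warns that market factors are controlled only if they do not strike one group alone when the intervention starts. That covers a price step at the start in general terms. It does not name drug prices and offers no remedy, and the table shows that steps at other dates also bias the estimate.

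Hypothesis 2 concerns what payers "will incur higher pharmaceutical spending, lower non-pharmaceutical cost growth, and lower overall cost growth", which means actual spending. Replacing it with standardised cost would change the question. This stands, so actual spending should remain the measure.

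A reader might infer more: that any price difference or change between the managers counts as an intervention effect, or that drug cost is wholly confounded. The documents do not support this. Constant gaps, common changes and steady earlier drift give exactly zero in the segmented model. A reader might also infer that the control-side contract changed, because CatalystRx is named as manager only at the time of initiation. The wording does not rule out a change, but it reports none. Nor should a price step be scaled against the 3.8-point detectable change in uptake, which is a power figure for users of a drug class and not an effect on spending.

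**Conclusion.** The point holds in limited form. For drug cost, manager and group coincide, and the described model has no term that separates a one-sided price step or trend break from the co-payment effect. The possible size equals the size of the break when it falls on the start date: 5% for an assumed 5%, with 2% to 10% as the range shown. At other dates the bias is spread over level and slope and may change sign. Overall cost carries a diluted version.

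This rests on three assumptions: that separate contracts allow separate prices, that Figure 2 has the standard segmented form, and that a break could occur. The documents give no contract price and report no repricing. Only secondary outcomes are exposed. This is a cheap improvement to the cost analysis, not a flaw in the primary comparison.

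**What to change.** 1. Keep actual spending as the measure for hypothesis 2.
2. Pre-specify a companion analysis with the same model in which every fill in both groups is valued at one fixed price list: the allowed amount per day of supply for each drug product, pooled over both managers in a pre-intervention base year. For products that enter later, use the first observed pooled price.
3. Attribute a difference in pharmaceutical or overall cost to the co-payment change only where the fixed-price result agrees. Where the two disagree, report the difference as including contract price.
4. Take the split between payer and patient from actual amounts only. Subtracting real co-payments from standardised prices would give a payer share that nobody paid.
5. In Study setting, limit the comparability statement to fills and days of supply.

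Cost: one price table built from claims already held, one additional analysis, and one reworded sentence. The fixed-price result reflects volume and product mix and is not in dollars actually paid, which is why it accompanies the actual-spending result and does not replace it.

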### Study population identification

The initial intervention population included 2,507 UM employees and dependents enrolled in UM's pharmacy benefits plan and identified as individuals with diabetes based on at least one pharmacy claim for a diabetic hypoglycemic medication (oral, injectable, or inhaled) within the 12 months prior to intervention.

The initial control population included 8,637 M-CARE enrollees receiving coverage through other employers and identified as individuals with diabetes using the same pharmacy claims criteria. Figure 1 depicts the intervention and control groups and their relationship to the University and M-CARE.

**Figure 1 F1:**
[figure not shown]
**Identification of intervention and control groups**. The large circle on the left (labeled 'U of M') depicts University of Michigan employees and dependants. The large circle on the right (labeled M-CARE) depicts M-CARE enrollees, with the central area of overlap representing UM employees enrolled in M-CARE. The subset of individuals with diabetes is depicted by the shaded circle labeled 'Diabetes.' The intervention group includes UM employees and dependents with at least one pharmacy claim for a glycemic medication (oral, injectable, or inhaled) within the 12 months prior to the study timeframe. The control group consists of M-CARE enrollees who are employees and dependents of other, non-UM employers with at least one pharmacy claim for a glycemic medication within the 12 months prior to the study timeframe.

While UM employee turnover is low, the population eligible for the intervention is not static. Both new UM employees with pre-existing diabetes and current employees newly diagnosed with diabetes are automatically enrolled in the intervention upon having an eligible pharmaceutical claim filed. The automatic enrollment design was chosen to reduce the burden of action required for individuals to benefit from the co-payment reductions. Participants could choose to opt-out of the program at any time. Further, UM employees and dependents not identified from pharmacy claims can opt-in to the program by contacting the Focus on Diabetes program coordinator and self-identifying that they have diabetes. While eligible for the full intervention, these 'opt-in' individuals will be excluded from analyses because there is no comparable control group.

